## Abstract

**Background:**

Coronary artery disease (CAD) remains one of the leading causes of mortality worldwide and is associated with multiple inherited and environmental risk factors. This study is designed to identify, design, and develop a panel of genetic markers that combined with clinical and angiographic information, will facilitate the creation of a personalized risk prediction algorithm (GEnetic Syntax Score—GESS). GESS score could be a reliable tool for predicting cardiovascular risk for future adverse events and for guiding therapeutic strategies.

**Methods:**

GESS (ClinicalTrials.gov Identifier: NCT03150680) is a prospective, non-interventional clinical study designed to enroll 1080 consecutive patients with no prior history of coronary revascularization procedure, who undergo scheduled or emergency coronary angiography in AHEPA, University General Hospital of Thessaloniki. Next generation sequencing (NGS) technology will be used to genotype specific single-nucleotide polymorphisms (SNPs) across the genome of study participants, which were identified as clinically relevant to CAD after extensive bioinformatic analysis of literature-based SNPs. Enrichment analyses of Gene Ontology-Molecular Function, Reactome Pathways and Disease Ontology terms were also performed to identify the top 15 statistically significant terms and pathways. Furthermore, the SYNTAX score will be calculated for the assessment of CAD severity of all patients based on their angiographic findings. All patients will be followed-up for one-year, in order to record any major adverse cardiovascular events.

**Discussion:**

A group of 228 SNPs was identified through bioinformatic and pharmacogenomic analysis to be involved in CAD through a wide range of pathways and was correlated with various laboratory and clinical parameters, along with the patients' response to clopidogrel and statin therapy. The annotation of these SNPs revealed 127 genes being affected by the presence of one or more SNPs. The first patient was enrolled in the study in February 2019 and enrollment is expected to be completed until June 2021. Hence, GESS is the first trial to date aspiring to develop a novel risk prediction algorithm, the GEnetic Syntax Score, able to identify patients at high risk for complex CAD based on their molecular signature profile and ultimately promote pharmacogenomics and precision medicine in routine clinical settings.

*Trial registration* GESS trial registration: ClinicalTrials.gov Number: NCT03150680. Registered 12 May 2017- Prospectively registered, https://clinicaltrials.gov/ct2/show/NCT03150680.

## Background

Coronary artery disease (CAD) is a complex, multifactorial disease driven by the cumulative and interactive modular effects of gene–gene, gene–environment and epigenetic interactions [1]. Notwithstanding intense investigation in the postgenomic era, the fundamental biological pathways underlying the multidecade process of atherosclerotic formation and chronic inflammation in CAD have not yet been addressed [2]. The need for unraveling the molecular and genetic underpinnings of CAD at a deeper level is stressed nowadays, due to exceptionally high mortality rates of CAD, despite the expanded arsenal of precision medicine [3]. Therefore, defining CAD will enable the treatment of patients on the basis of a better understanding of their clinical presentations.

The potential for genotype-guided precision medicine is pointed out by recently emerging evidence from large scale studies investigating various gene expressions in patients with CAD. Hitherto, several Genome-Wide Association Studies (GWAS) have mapped more than 150 single-nucleotide polymorphisms (SNPs) potently implicated in CAD pathogenesis [1, 4–7]. These candidate variants are not yet established though and as Next Generation Sequencing (NGS) becomes the heart of high-throughput genotyping technologies, several plausible genetic variants linked with multifactorial traits of CAD might be discovered, shedding light on the road of personalized medicine [8]. Meanwhile, significant therapeutic implications emerge from the integration of genetic data into predictive risk scores. Specifically, several studies have been envisaged, in order to correlate distinct genetic variants with modulation of the risk for CAD occurrence or progression [9–11]. In those studies the severity of CAD has been assessed via clinical, laboratory or imaging parameters, but not with the Synergy Between Percutaneous Coronary Intervention With Taxus and Coronary Artery Bypass Graft Surgery (SYNTAX) score yet [12–15].

The SYNTAX score is the best-known scoring algorithm to evaluate CAD complexity as a comprehensive angiographic grading tool taking into consideration anatomic risk factors [16]. According to the extent of CAD, this score facilitates the objective guidance of decision-making between coronary artery bypass grafting (CABG) surgery and percutaneous coronary intervention (PCI). Despite, the SYNTAX score relies on invasive coronary angiography findings and the discovery of risk stratification algorithms that facilitate non-invasive estimation of CAD complexity could alter the prognostic plan in patients with CAD.

The rationale behind this prospective study is to associate, for the first time, the severity of CAD, as assessed by the SYNTAX score, with patients’ genomic profile in a real-world setting of patients undergoing coronary angiography [16]. The desirable goal is to corroborate genomic and pharmacogenetic research on CAD exploring the potential clinical association of 228 selected SNPs with CAD and individualized response to clopidogrel and statin therapy, which could disentangle gene expression alterations in blood of patients with CAD. Ultimately, the GESS trial aspires to develop a genetic SYNTAX score that could non-invasively enable the identification of patients with complex and severe CAD after a blood-based gene expression analysis. This study is designed to contribute to recent calls for implementing genotype-guided precision medicine decisions, by aiding the clinicians to achieve improved prediction and therapy outcomes for CAD patients [3].

## Methods

### Study design and population

GESS (ClinicalTrials.gov Identifier: NCT03150680) is an ongoing prospective, single‐center, cohort study enrolling patients undergoing coronary angiography.

Ethical approval was obtained from the Scientific Committee of AHEPA University Hospital (reference number 309/11–05-2017). Written informed consent will be obtained from each patient prior to study enrollment and the trial procedures conform with the Declaration of Helsinki [17].

GESS study is designed to enroll 1080 consecutive adult patients admitted to AHEPA University Hospital of Thessaloniki, Greece and undergoing coronary angiography for clinical purposes. Coronary angiography can be performed either on an emergency basis or scheduled. For the purpose of this research, patients with history of prior percutaneous coronary intervention or coronary artery bypass grafting and patients unwilling to provide informed consent will be excluded from the study. The selection criteria of the study are presented in detail in Table 1.

**Table 1 Tab1:** Eligibility criteria for the enrollment in the GESS study

Inclusion criteria	Exclusion criteria
Patients undergoing coronary angiography	Medical history of prior coronary revascularization procedure
Age > 18 years old	Cardiopulmonary arrest at admission
Informed consent for study participation	Severe concurrent disease with life expectancy less than 12 months

Pre-specified clinical data, including demographic characteristics, medical history, medication and clinical presentation will be recorded for the entire study population by research study coordinators under standardized methods. Accordingly, study participants will be classified into 3 main subsets, based on their clinical presentation: 1. patients undergoing preoperative coronary angiography without symptoms suggestive of CAD, 2. patients with chronic coronary syndrome, and iii. patients with acute coronary syndrome.

### Genotyping and bioinformatic analysis

Peripheral whole blood will be collected and labeled with a unique barcode to ensure anonymization and unbiased assessment. High quality genomic DNA will be extracted using commercial kits (Qiagen) and will be quantified by spectrophotometry using Nanodrop 1000 (Thermo Fisher). Ultrasensitive targeted NGS of extracted DNA (40 ng) will be performed using custom QIAseq Targeted DNA Panel (Qiagen) containing primers for the enrichment of the 228 SNPs of interest. The produced molecularly barcoded libraries will be quantified by Qubit 3 Fluorometer (Invitrogen) and real time PCR (QIAseq Library Quant Assay kit). Sequencing will be performed by sequencing by synthesis (SBS) chemistry on MiniSeq Platform of Illumina using the MiniSeq Mid Output Kit (300-cycles). The generated NGS data (in fastq format) will be analyzed with the CLC Genomics Workbench (Qiagen) bioinformatics software and the genotype of each SNP will be determined.

### Biostatistics and disease ontology enrichment analysis

We sought to identify genes whose coding sequence and/or expression levels are affected by the selected 228 SNPs studied here. To this end, data mining was performed from dbSNP database using reutils [19, 20]. In addition, further information on genes, associated with the selected SNPs through GWAS, were retrieved from HumanMine database [21] using InterMineR [22]. Our approach led to the formation of a list with 127 genes that have been associated with the selected SNPs. Next, enrichment analysis was performed to identify statistically significant disease terms, whose involved genes are overrepresented in our gene list. Enrichment analysis, with Benjamini–Hochberg adjusted *p-value* < 0.001, was performed using clusterProfiler [23] and DOSE [24] (Figs. 1 and 2).

**Fig. 1 Fig1:**
[figure not shown]
Barplot of top 15 statistically significant disease ontology terms. Disease terms and number of genes are displayed in y and x axis, respectively. Enrichment analysis and barplot creation were performed using clusterProfiler and DOSE

**Fig. 2 Fig2:**
[figure not shown]
Gene concept network of top 15 statistically significant disease ontology terms. Enrichment analysis and network creation were performed using clusterProfiler and DOSE

### Statistical considerations

#### Sample size estimation and endpoints of the study

The primary endpoint of the study is to discover potential correlations of the SYNTAX score with patients' genomic profile and create a blood-based gene expression test (genetic SYNTAX score) which could accurately identify patients at high risk for CAD of moderate or high severity. For the estimation of the sample size the G*Power [25, 26] and Epi Info (StatCalc) [27] software tools were used. To this regard, we made use of the exact sampling distribution of the squared multiple correlation coefficient implemented in G*Power assuming 250 predictors, a two-tailed test, power of 0.9, significance level of 0.05, ρ^2^ = 0.13 and a ratio of unexposed to exposed equal to 2 (based on a pilot study on 100 patients). The initial sample size was finally increased by 10% because of the possibility that some patients might be lost to follow-up. Hence, we aim for a total sample of 1080 patients.

Secondary endpoints of the study are the development of a panel of genetic markers that, in conjunction with clinical parameters, could strongly predict the occurrence of MACCE or any bleeding events during follow up.

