### Statistical analysis

Descriptive analysis will be used to summarize the data. Specifically, results will contain statistics as mean, standard deviation, median, minimum and maximum values, whereas for categorical variables the frequency distribution tables with number of cases and percentage distribution will be presented. Statistical hypothesis testing procedures (*Kolmogorov–Smirnov* and *Shapiro–Wilk*) will be conducted for continuous variables to check, whether they satisfy the normality assumption. Given the fact that the response variable (SYNTAX score) presents a heavily-skewed and non-normal distribution with an excess number of zeros, non-parametric statistical hypothesis tests will be used for the investigation of the main effects of categorical variables on the population median values of the response variable. More specifically, the *Mann–Whitney* and *Kruskal–Wallis* followed by pair-wise comparisons through Mann–Whitney test using *Bonferroni’s correction* will be conducted. The investigation of the relationship between SYNTAX score and the set of continuous variables will be performed using the non-parametric *Spearman’s correlation coefficient*.

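### The stated sample-size inputs lead to about 788 patients, not 1080, so the plan's power, effect size and N do not belong together

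*Protocol article*

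**What the plan says.** Under 'Sample size estimation and endpoints of the study', the protocol article names G*Power and Epi Info (StatCalc) as its tools. For the method it says "we made use of the exact sampling distribution of the squared multiple correlation coefficient implemented in G*Power". The inputs are "assuming 250 predictors, a two-tailed test, power of 0.9, significance level of 0.05", a ρ² of 0.13, and an unexposed-to-exposed ratio of 2, with a pilot study of 100 patients cited as a basis.

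The text then says "The initial sample size was finally increased by 10% because of the possibility that some patients might be lost to follow-up" and concludes "Hence, we aim for a total sample of 1080 patients".

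The primary endpoint in the same section is the correlation of the SYNTAX score with the genomic profile, and a test that accurately identifies patients at high risk of moderate or severe disease. Under 'Study design and population', blood is drawn on the enrolment day before angiography, and the SYNTAX score is read from the angiogram. The one-year telephone call collects symptoms, MACCE and bleeding.

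Under 'Statistical analysis', the SYNTAX score "presents a heavily-skewed and non-normal distribution with an excess number of zeros". The planned methods are Mann–Whitney, Kruskal–Wallis and Spearman analyses, then a two-part hurdle model with predictors removed by AIC.

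**The concern.** The section gives what reads as a complete input list for one named procedure and presents 1080 as its result. If the inputs do not lead there, a reader cannot tell what effect 1080 patients were meant to detect, or with what power.

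Three further features point the same way:

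- The exposure ratio has no role in a single-sample test of R².
- Loss to follow-up cannot remove a patient from a primary analysis whose outcome and genotype are both obtained around enrolment.
- The powered test is an overall test in a normal linear regression. The analysis section describes rank tests and a hurdle model for a zero-heavy score, and no overall R² test.

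At stake is the only quantitative justification offered for the primary endpoint.

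**Working it through.** **Inputs from the sample-size section.** Predictors k = 250 ("assuming 250 predictors"); "a two-tailed test"; "significance level of 0.05"; power 0.90; ρ² = 0.13; inflation 10%; stated total 1080. **Assumed:** the null value is ρ² = 0, since the article does not state one.

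**Formula.** Given the predictors, F follows a noncentral F distribution with k and N − k − 1 degrees of freedom and noncentrality λ = f² × χ²(N − 1), where f² = ρ²/(1 − ρ²) = 0.13/0.87 = 0.149. Power is the rejection probability averaged over the chi-square. The required N is the smallest that reaches 0.90.

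**Step 1: attempt to reproduce 1080.**

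| Test | N | Denominator df | Upper critical F | Mean λ = f²(N − 1) | Power | N × 1.10 |
|---|---|---|---|---|---|---|
| Two-tailed, 0.025 per tail (as stated) | 716 | 465 | 1.239 | 106.8 | 0.900 | 787.6, so 788 |
| Upper tail only, 0.05 | 657 | 406 | 1.203 | 98.0 | 0.901 | 722.7, so 723 |

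One patient fewer falls just below 0.90 in both rows. The stated total is not reproduced: 1080/788 = 1.37 and 1080/723 = 1.49, so it is 37% to 49% above what the inputs give.

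**Step 2: other plausible readings.**

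- Inflating by division: 716/0.9 = 795.6, so 796; 657/0.9 = 730.
- Fixed-predictor F test, upper tail: N = 653, or 719 after the 10% increase.
- 228 predictors (the SNPs alone): 681 two-tailed or 623 upper-tail, giving 750 or 686 after the increase.
- Reading 0.13 as f² instead of ρ²: 797 or 728. Multiplying by 1.10 gives 876.7 or 800.8, so 877 or 801.

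None comes close to 1080.

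**Step 3: work back from 1080.** The base is 1080/1.10 = 981.8, about 982.

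| N | Power at ρ² = 0.13, two-tailed | Power at ρ² = 0.13, upper tail | ρ² detectable at 90% power, two-tailed | ρ² detectable at 90% power, upper tail |
|---|---|---|---|---|
| 982 | 0.995 | 0.998 | 0.091 | 0.082 |
| 1080 | 0.9987 | 0.9995 | 0.082 | 0.074 |

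So 1080 matches the stated 90% power only for an effect clearly smaller than 0.13.

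**Step 4: the ratio.** The formula in Step 1 uses N, k, ρ², α and the number of tails. It has no place for a ratio of exposure groups. Such a ratio belongs to a two-group calculation, which Epi Info could have supplied, but the article gives no risks, odds ratio or other input for one.

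**Step 5: the 10%.** Genotype comes from enrolment blood and the SYNTAX score from the study angiogram. A missed telephone call one year later affects MACCE and bleeding, which are secondary endpoints. Primary-analysis losses would come from unusable genotype or angiogram data.

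**Step 6: the analysis.** The power figure is for rejecting ρ² = 0 across all predictors jointly in a linear model. The 'Statistical analysis' section describes rank tests, Spearman correlation and an AIC-selected hurdle model judged by error metrics, classification metrics and cross-validation. Power for the hurdle model cannot be computed from the article, because the zero fraction, dispersion and SNP effects are not given.

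**The case against.** The strongest reply is that nothing shows an arithmetic error. The article names two programs and lists a cohort-type ratio, so a second calculation was probably run, and 1080 may come from it. A journal article condenses, and those inputs may sit in the full protocol. This stands, and it limits the point to a mismatch between what is stated and the total claimed for it. It does not remove the point, because the article ties 1080 to the R² inputs.

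A reader might try to find what was really run. Using only the upper-tail 657 as the unexposed group gives 657 × 1.5 × 1.10 = 1084. A two-tailed α of 0.001 gives 982 before inflation, hence 1080. These routes are incompatible and each departs from the text, so neither is evidence.

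A reader might also infer that the study is underpowered. The documents show the opposite for the stated test: power at 982 is at least 0.99. Recruitment had already reached 783 by November 2020, close to the 788 the inputs require.

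Planning on a linear R² approximation and then fitting a more suitable model is common, and an overall association test does address the correlation part of the primary endpoint. This also stands. An analysis plan not shown here might contain such a test, so the claim is only that this article describes none. What remains is that the approximation should be labelled as one.

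Finally, allowing for loss to follow-up is sensible for the secondary endpoints. Only its use as the sole reason for the primary sample size is misplaced.

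**Conclusion.** The point holds as a reporting inconsistency of moderate importance. The stated inputs give 788 patients after inflation for the two-tailed test as written (723 for the upper tail alone), against a stated 1080. At the implied base of 982 the power is about 0.995 to 0.998, not 0.90. The result assumes a null of ρ² = 0, and no standard variant that was tried closes the gap.

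The cause cannot be settled from the article, and the discrepancy adds patients rather than removing them. It therefore does not threaten the stated test. Rejecting ρ² = 0 would also not show that the score identifies patients accurately, so the power figure should not be read as support for that part of the primary endpoint.

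**What to change.** Keep 1080 and restate its justification:

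1. Report the calculation that produced 1080, with every input. Otherwise state that 1080 enrolled, with about 982 evaluable, give more than 99% power for ρ² = 0.13 with 250 predictors. Add that the ρ² detectable at 90% power is about 0.082 to 0.091 at 982 (0.074 to 0.082 at 1080), the lower value being upper-tail and the higher two-tailed. State the null value and the tails used.
2. Remove the unexposed-to-exposed ratio, or attach it to the calculation it belongs to.
3. Link the 10% for loss to follow-up to the secondary MACCE and bleeding endpoints. Base any allowance for the primary endpoint on the expected share of unusable genotype or angiogram data.
4. Say that the power figure is for an overall linear R² test used as a planning approximation, and that it describes neither the hurdle-model analysis nor the accuracy of the score.

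The cost is a rewritten paragraph. No patients, visits or analyses are added.

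### The stated 90% power belongs to a joint test of 250 predictors, so it is not established for the genomic association that is the primary question

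*Protocol article*

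**What the plan says.** In the protocol article, under *Sample size estimation and endpoints of the study*, the statement of the primary aim opens: "The primary endpoint of the study is to discover potential correlations of the SYNTAX score with". The object of that sentence is the genomic profile, and it goes on to the building of a genetic SYNTAX score. The same paragraph names its sizing tool as the "exact sampling distribution of the squared multiple correlation coefficient implemented in G*Power". The inputs fed to that tool are then listed, beginning: "assuming 250 predictors, a two-tailed test, power of 0.9, significance level of 0.05". The effect size is a squared multiple correlation of 0.13, and a 2:1 ratio of unexposed to exposed is added; a pilot of 100 patients is cited as the basis. The result was raised by a tenth to allow for losses during follow-up, which leads to the target: "Hence, we aim for a total sample of 1080 patients".

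Under *Genotyping and bioinformatic analysis*, the sequencing panel is described as "containing primers for the enrichment of the 228 SNPs of interest". The abstract, background and discussion also give 228.

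The article does not say which predictors make up the 250 or how the 0.13 divides between SNPs and anything else. The *Statistical analysis* section plans univariable rank tests and correlations. It then plans a hurdle model with backward selection by AIC, assessed by fit and cross-validated prediction. It describes no joint test of the SNPs.

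**The concern.** The test used for sizing has one null hypothesis: none of the 250 predictors carries information on SYNTAX. That null is false as soon as any one of them is related to the score. If the 250 include age, sex or other clinical variables, a significant result would not show a genomic correlation.

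The reverse risk also matters. A reader will take 0.9 as the chance of detecting a genomic association if one exists. A null genomic result could then be read as good evidence of absence, when the actual power might be far lower. The quantity that matches the primary question is the power to detect what the 228 SNPs add to the other predictors.

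**Working it through.** **Inputs from the article.** 250 predictors; ρ² = 0.13; α = 0.05, two-tailed; power 0.9; 10% increase; total 1080; 228 SNPs.

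**Inferred or assumed.**
- Predictors beyond the panel: 250 − 228 = 22, taken here as clinical variables.
- Null value ρ² = 0.
- Sample before the increase: 1080/1.1 ≈ 982.
- Clinical R² is not given, so it is varied from 0 to 0.13 with the total held at 0.13.

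**Method.** In the exact random-predictor model with N patients and p predictors, R² given k follows Beta(p/2 + k, (N − p − 1)/2). Here k is negative binomial with size (N − 1)/2 and success probability 1 − ρ². The two-tailed test puts 0.025 in each tail of Beta(p/2, (N − p − 1)/2).

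**Step 1, the plan's own figure.** With p = 250, ρ² = 0.13 and 90% power, the exact two-tailed test needs N = 716, and 716 × 1.1 = 788. One-tailed it needs 657, and 657 × 1.1 = 723. Neither gives 1080. At N = 982 the joint test has 99.5% power at ρ² = 0.13. The steps below use 982 because it is the size the article implies.

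**Step 2, rejection of the joint null when no SNP matters.** Here ρ² equals the clinical R², with p = 250 and N = 982.

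| Clinical R² | Probability of rejection |
|---|---|
| 0.05 | 45% |
| 0.08 | 82% |
| 0.10 | 94% |
| 0.13 | 99.5% |

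**Step 3, power for the SNP block.** Let d be the SNP share, so the clinical R² is 0.13 − d. The partial squared correlation of the SNPs given the other 22 is d / (1 − (0.13 − d)) = d / (0.87 + d). The same exact test is applied with p = 228 and N reduced by 22, to 960. For example, d = 0.05 gives 0.05/0.92 = 0.0543.

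| SNP share d | Partial ρ² | Power, two-tailed |
|---|---|---|
| 0.02 | 0.0225 | 14% |
| 0.03 | 0.0333 | 25% |
| 0.05 | 0.0543 | 54% |
| 0.065 | 0.0695 | 73% |
| 0.08 | 0.0842 | 87% |
| 0.10 | 0.1031 | 96% |
| 0.13 | 0.13 | 99.6% |

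**Step 4, share needed for 90%.** Solving step 3 for 90% power gives d ≈ 0.084, which is 0.084/0.13 ≈ 65% of the assumed total. With the whole 0.05 in the upper tail, d ≈ 0.075, or about 58%.

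**Step 5, dependence on 982.** At N = 716, the size that does give 90% joint power, SNP-block power is 91% if the SNPs carry all of the 0.13. It is 75% if they carry 0.10 and 44% if they carry 0.065.

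**The case against.** The strongest reply is that the 22 clinical predictors are nowhere stated. The figure of 250 could be a rounded allowance above 228 or could reflect genotype coding. If all 250 terms are genomic, the joint test is the genomic test and the mismatch disappears. An itemised predictor list is also something an article may leave to the full protocol. This stands as a limit on the point. It does not remove it, because the article attaches the 0.9 to its primary endpoint without saying what the 250 are.

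Two stronger readings are tempting, and the documents support neither:
- **That clinical variables alone would reject the null.** The article gives no clinical R². At 0.05 the rejection probability is only 45%, so the supportable word is *could*.
- **That genomic power is not 90%, or is below it.** The direction is unknown. Power exceeds 90% once the SNP share passes about 0.084, and the unseen split of the 100-patient pilot may be largely genetic.

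It is also fair to say that an R² calculation is only a sizing approximation. The article itself calls SYNTAX heavily skewed with excess zeros and plans a hurdle model, so adding a linear block test would fit poorly. That objection stands, and it bears on how the fix is framed: the comparison belongs inside the hurdle model.

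**Conclusion.** The point holds in a limited form. The stated power refers to a joint null on 250 predictors, and rejecting that null would not isolate a genomic effect if some of them are clinical. The planned analyses contain no joint test that does isolate it. The 90% is therefore not established for the primary question.

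Across SNP shares of 0.03 to 0.10, power for that question runs from 25% to 96%. Roughly two-thirds of the assumed 0.13 must come from the SNPs to reach 90%.

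These figures rest on 22 non-SNP predictors, a null of ρ² = 0, 982 evaluable patients and a linear-model approximation. The separate fact that the stated inputs give 788 and not 1080 does not remove the concern, as the figures at 716 patients show.

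**What to change.** 1. State what the 250 predictors are and, if the pilot allows, how much of the 0.13 is attributed to SNPs.
2. Within the planned hurdle model, add a comparison of the full model (clinical plus SNP) with the clinical-only model, and name it as the joint test of genomic association.
3. Restate the power for that SNP block over a range of SNP shares of the 0.13, using the stated exact two-tailed method and labelling it a linear-model approximation. Possible wording: *With 982 evaluable patients and a total ρ² of 0.13, 90% power for the 228 SNPs given 22 other predictors requires the SNPs to explain about 0.084; at shares of 0.05 and 0.065 the power is about 54% and 73%.*

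Enrolment stays as planned. The cost is one added analysis, one recalculation, some wording, and a stated power that may look less favourable.
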